**Figure 1 F1:**
[figure not shown]
Test and control areas of the study.

The Social Marketing Campaign consists of three ways; firstly, by a Communication Campaign in the two Test Areas using advertisements developed and posted in the local print media. Secondly, flyers have been designed to be distributed by our local partners. Finally, conferences for older people will be organized in the test areas to reach the target audience for this program.

Finally, to encourage people to participate in this PA program, a gift card worth 20 € will be distributed to participants at registration. Then, a second gift card worth € 20 will be distributed to those who carry out at least 10 sessions out of the 12 offered. This study will last for 18 months. The study is underway and started in March 2020. The study flow-chart (Figure 2) summarize the study.

**Figure 2 F2:**
[figure not shown]
Flow-chart of the study.

### Recruitment in the Test Area

#### Selection

Individuals in the study areas who have seen the advertisement for the Balance Workshops and who fulfill the inclusion criteria will be eligible for the study. They will contact our partners (“Atouts Prévention” and “Association Régionale Santé Prévention sur les Territoires Auvergne” through the contact details provided alongside the advertisements) to register for the workshops organized by the French Federation of Physical Education and Voluntary Gymnastics (FFPEVG) at the local level.

#### Registration

During the first session, each study participant will be given an Information Sheet as well as a 20 € gift card. A computerized data collection tool designed for the study and allowing for the constitution of the database will be available during the collection phase from the first session of the workshops and then 6 months after inclusion.

#### Follow-Up

Those who consent to participate in the study will go through all the sessions for the 12 weeks. Gift cards will be distributed to those who complete 10 of the 12 sessions. During the 1st and 12th sessions, the FFPEVG organizers will collect the previously mentioned data from the study participants. Finally, 3 months after the end of the Balance Workshop sessions, participants will be contacted by the Principal Investigator by telephone to collect the same data.

### Recruitment in the Control Area

#### Selection

In the same way as when registering people for the Balance Workshops, the FFPEVG of the Rhône will contact older people who meet the inclusion criteria.

#### Registration

During the first session, each study participant will be given an Information Sheet. A computerized data collection tool designed for the study and allowing for the constitution of the database will be available during the collection phase from the first session of the workshops and then 6 months after inclusion.

#### Follow-Up

Those who consent to participate in the study will go through all the sessions for the 12 weeks. During the 1st and 12th sessions, the FFPEVG organizers will collect the previously mentioned data from the study participants. Finally, 3 months after the end of the Balance Workshop sessions, the Principal Investigator will contact participants by telephone to collect the same data.

#### End of Study

The end of the study for the participants will be marked by the completion of the telephone interview 3 months after the end of a cycle of Balanced Workshops.

##### Duration of Participation in the Study

An average of 6 months per participant.

#### Inclusion Criteria

- Individuals aged 60 and over- Individuals living in the Loire, Haute-Loire or Rhône Regions of France- Individuals who do not have medical contraindications concerning participation in moderate PA- Individuals who have been fully informed about the study, including their rights over the data to be collected

#### Non-inclusion Criteria

- Persons unfit to participate in Balance Workshop sessions- Persons already enrolled in a similar PA

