#### Evaluation Criteria

The primary endpoint is the attendance rate of the participants in the Balance Workshop sessions for fall prevention. The secondary evaluation criteria are the number of calls received for a registration request, the evolution of the level of the quality of life using the SF 36 questionnaire (42, 43) and the evolution of the level of PA of the participants using the short version of the IPAQ questionnaire for older adults (44).

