## Statistical Analyses

### Number of Participants Required

In the Balance Workshops carried out by the “Caisses d'Assurance Retraite et de la Santé au Travail” (CARSAT) for the Loire and Rhône Regions in 2018, about 43% of those who registered went through the 12 sessions. Attendance was at 44% in the Loire Region and 42% in the Rhône Region. In our study, we hope to raise the attendance by about 20%, to get to 63% per group who go through the 12 sessions.

We compared two binomial proportions observed with:

$$\begin{array}{l} \text{π}1=0\text{.}43\text{ π}2=\;0\text{.}63\\ \text{α}=5\%\;Power1-\text{β}=\;0\text{.}9 \end{array}$$

The total number of participants required is 210 (with 105 for the Test Area and 105 for the Control Area).

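### Former Balance Workshop participants can enter the study, and previous participation is not a listed variable, so an imbalance between areas on a likely predictor of attendance could not be properly adjusted for

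*Protocol article*

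**What the plan says.** There are two Non-inclusion Criteria: "Persons unfit to participate in Balance Workshop sessions" and "Persons already enrolled in a similar PA". The Inclusion Criteria add age, residence, absence of a medical contraindication and having been informed. None of them mentions an earlier Balance Workshop cycle, a minimum interval since one, or a single entry per person.

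The two arms recruit by different routes. For the Test areas, the Selection paragraph states: "Individuals in the study areas who have seen the advertisement for the Balance Workshops and who fulfill the inclusion criteria will be eligible". It continues: "They will contact our partners". For the Control area, the Selection paragraph opens "In the same way as when registering people for the Balance Workshops" and then says that "the FFPEVG of the Rhône will contact older people who meet the inclusion criteria". It does not say where those contacts come from.

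Under Evaluation Criteria, "The primary endpoint is the attendance rate of the participants in the Balance Workshop sessions for fall prevention". The sample size section takes its planning rate from 2018 workshops in Loire and Rhône, where "about 43% of those who registered went through the 12 sessions" (44% in Loire, 42% in Rhône).

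Recorded Variables and Source Data lists sociodemographic items, attendance, how the person heard of the workshops, the EPICES score, SF-36 and IPAQ. Previous workshop participation is not on the list.

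**The concern.** The primary endpoint is a behaviour: coming to the sessions. Whether a person has already been through the same programme is a plausible predictor of that behaviour, and possibly a strong one. Former participants exist, since the sample size section relies on workshops held in 2018.

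In a randomised trial this would matter little. Here the study designers chose which areas are Test and which is Control, and the Design and Setting section rests its causal argument on a comparison group whose initial characteristics resemble those of the Test group. An advertisement answered by residents and contact made by the provider need not bring in the same mix of newcomers and former participants. If the mix differs, part of the difference in attendance between areas reflects who entered and not what the campaign did.

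An analysis plan can choose covariates later, but it cannot adjust for something that was never collected. That makes this a point for the data collection list and not a detail to be left to the analysis plan.

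**Working it through.** **1. Reading the criteria.** Taken literally, the second non-inclusion criterion removes people who are in a similar activity when they register. A person who finished a cycle in 2018 or 2019 passes every listed criterion. So does a person whose first study cycle has ended and who registers for another.

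**2. Room for a second entry.** The study lasts 18 months, but Ethical Considerations puts data collection from September 2020 to July 2021, about 11 months. Participation averages 6 months, so two full participations need 2 × 6 = 12 months and do not quite fit. Two cycles alone need 2 × 12 = 24 weeks and do fit, with the second overlapping the first telephone follow-up. Re-entry is possible, but the article gives no sign that it would be common.

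**3. The plan's own figure.** Inputs from Number of Participants Required: π1 = 0.43, π2 = 0.63, α = 5%, power 90%, 105 per area. With p̄ = 0.53, pooled variance and no continuity correction,

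n = [z_α √(2p̄(1−p̄)) + z_β √(π1(1−π1) + π2(1−π2))]² / (π2−π1)²

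- One-sided: [1.645 × 0.7058 + 1.282 × 0.6915]² / 0.04 = 104.8, so 105 per area and 210 in total. This reproduces the plan.
- Two-sided: [1.960 × 0.7058 + 1.282 × 0.6915]² / 0.04 = 128.8, so 129 per area.

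At 105 per area, power is 90% one-sided and 83% two-sided. The article does not state the sidedness. That is a separate matter, so both versions are shown below.

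**4. Form of the bias.** Let q_T and q_C be the shares of former participants in the Test and Control areas, and d their extra completion over newcomers. The distortion of the Test-minus-Control difference is (q_T − q_C) × d. It is zero if the shares are equal, negative if Control has more, and positive if Test has more.

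**5. Illustration, one direction only.** Assumptions not in the article: former participants sit only in Control, newcomers in Control complete at 43%, Test stays at 63%, participants are independent, 105 per area. Control rate = 0.43 + q_C × d.

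| Share q_C | Completion of former participants | Control rate | Difference | Power, one-sided | Power, two-sided |
|---|---|---|---|---|---|
| 0% | – | 43.0% | 20.0 | 90% | 83% |
| 10% | 63% | 45.0% | 18.0 | 84% | 75% |
| 20% | 63% | 47.0% | 16.0 | 76% | 65% |
| 30% | 63% | 49.0% | 14.0 | 66% | 53% |
| 10% | 80% | 46.7% | 16.3 | 77% | 66% |
| 20% | 80% | 50.4% | 12.6 | 58% | 45% |
| 30% | 80% | 54.1% | 8.9 | 37% | 26% |

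Over this range the distortion runs from 0.10 × 0.20 = 2 points to 0.30 × 0.37 = 11.1 points. Had the same shares been in the Test areas only, the same 2 to 11.1 points would be added to the campaign's apparent effect.

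**6. What the table cannot show.** The 2018 rate is among all who registered and is not limited to newcomers. If repeat attenders were among them, 43% already contains their contribution, and only a share above the 2018 level would move the Control rate. The article gives neither that share nor the completion rate of former participants.

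**The case against.** A reader might infer that the Control route favours former participants, because the provider would contact people it already knows, and that the campaign effect is therefore diluted. The article does not support this. It names no source for the Rhône contacts, describes the route as the usual way of registering people, and leaves open that eligibility is checked after contact. Nor does it say that Test recruits are new to the workshops. Former participants in Loire or Haute-Loire could equally respond to the advertisements, flyers, conferences or the 20 € card. Dilution, inflation and no distortion all remain open.

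A reader might also infer that people will be counted twice. As shown above, the collection window leaves little room for two full participations, and the full protocol may deal with duplicate registrations.

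Three further objections carry some weight. The item on how people heard of the workshops could identify some former participants, though only as a proxy: someone who attended before may still name the advertisement. The full questionnaire is not shown and may contain the missing item. Finally, the main objective concerns people aged 60 and over, not first-time participants, so admitting former participants is a defensible choice.

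What stands is narrower. Former participants are eligible, the listed variables do not identify them directly, and the areas recruit by different routes in a comparison without randomisation. None of that depends on the direction of any imbalance.

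**Conclusion.** The point holds as a gap in eligibility wording and in the variable list, with a possible confounder that the listed variables capture at best by proxy. It does not hold as a demonstrated bias towards either area. The conclusion rests on a literal reading of the criteria, on the listed variables being those collected, and on the assumption that earlier participation predicts attendance. The 2 to 11 points and the associated power losses are an illustration under assumed shares and completion rates. This is a cheap improvement worth making, not a flaw that invalidates the design.

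**What to change.** - Add one yes/no item at session 1, worded identically in Loire, Haute-Loire and Rhône, on whether the person has taken part in a Balance Workshop cycle before.
- Adjust the primary comparison for it, for example as a covariate in the generalized linear model already named under Multivariate Analyses, and report newcomers separately.
- State that each person counts once, at the first inclusion only.

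The cost is one extra question and one extra covariate. Excluding all former participants is optional and carries its own price: it narrows the population and may make the 2018 planning rate of 43% inapplicable if that rate includes repeat attenders.

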#### Partial or Permanent Exclusion Criteria

All participants will be free to cancel the full recording of their data or stop some particular recording in progress. This will be considered as change of opinion or refusal of data transfer. In such a case, the data will not be taken into account and the participant will be classified among the premature stopping of the study by withdrawal.

#### Evaluation Criteria

The primary endpoint is the attendance rate of the participants in the Balance Workshop sessions for fall prevention. The secondary evaluation criteria are the number of calls received for a registration request, the evolution of the level of the quality of life using the SF 36 questionnaire (42, 43) and the evolution of the level of PA of the participants using the short version of the IPAQ questionnaire for older adults (44).

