Although this method has proven its worth in these other contexts, its use in getting older adults to take part in regular PA remains limited (41).

The main objective of this study is to determine whether associating a Social Marketing program would increase the attendance rate of people aged 60 and over in Group Balance Workshops.

The secondary objectives of this study are: (1) to increase the participation rate in the Balance Workshop sessions, (2) to increase the level of the quality of life of the participants, and (3) to increase the level of PA among the people participating in the study.

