#### Recorded Variables and Source Data

Data will be collected directly from the questionnaires as the study progresses.

The information collected on the participants will include:

- Sociodemographic characteristics: Age, subjective age, sex, level of education, family situation, living conditions- Attendance and participation rates in the workshops- How they got to know about the Balance Workshops.- Individual Precariousness Index - Evaluation of the Deprivation and Inequalities of Health in Healthcare Centers (EPICES) Score: This assessment is made up of 11 questions that summarize the precarious situation of a person. A coefficient is assigned to each response, the sum of which gives the EPICES score which is continuous, and varies from zero (lack of precariousness) to 100 (maximum precariousness). The evaluation of this score has been relevant in detecting and quantifying precariousness. A value of 30 is considered as the Precariousness Threshold according to EPICES (45).- Level of quality of life: Questionnaire SF 36 is the generic questionnaire most often used in Medicine for the evaluation of the quality of life in general. It analyzes the physical, emotional and mental dimensions. The full version includes 36 questions (42, 43). A score for each dimension of the SF-36 is calculated, ranging from 0 to 100. Poor health, loss of function, and presence of pain were scored as low. Good health, absence of functional deficit and pain were scored as high.- Level of PA: IPAQ Questionnaire - E is a short version of the International Physical Activity Questionnaire for older adults. It was validated for the assessment of the level of PA in older adults and has seven questions that classify them at various levels of PA (44). Official IPAQ guidelines (46) are as follows: data are added “*within each item (i.e., vigorous intensity, moderate intensity, and walking) to estimate the total amount of time spent engaged in PA per week. Total weekly PA (MET-min week*−*1) was evaluated by adding the products of reported time for each item by a MET value, specific to each category of PA*” (46). “*MET values were assigned as projected for use with elderly adults: vigorous PA* = *5.3 METs, moderate PA* = *3.0 METs, and walking* = *2.5 METs*” (47).

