This study brings together a provider (the FFPEVG) and promoters (“Atout Prévention Rhône-Alpes” and ARSEPT Auvergne) which, in this case, are medico-social groups. Currently, the locations where the Balance Workshops take place belong neither to the provider nor to the promoters. To facilitate the setting up of these structures in our areas of intervention, we established collaborations with the City or Community Social Action Centers, which have rooms and gymnasia for such purposes. This joint collaboration between these various groups in these regions will provide a global solution to encourage older adults to move toward PA centered on balance.

Accessibility to the workshops, whether physical and/or financial, is an essential condition for the participation of older adults in these activities (52). This study will lead to the establishment of new workshops in all these areas of intervention, thus making the product more accessible to the target audience. Also, even if this Balance Workshop program is free in one region and costs very little in another, we wanted to offer incentives to be able to deepen our knowledge of their capacity or not to increase participation in our program.

The adaptation of the program to the needs and expectations of the older adults is also a condition that favors their participation (52). That is why we interviewed some of them to identify these issues and improve on our program. From the survey, we developed an intervention strategy that included appropriate communication with them (modification of communication tools and use of new media validated by them) and training of professionals with particular emphasis on the fears and expectations of their trainees.

We equally chose geographic segmentation. The Loire and Haute-Loire (Test) Regions will receive the marketing campaign, but not the Control Area (Rhône Region). These are neighboring Regions, so this introduces a bias in our study. Therefore, those who will run the program particularly in the Control Area, may have to make more efforts to increase participation in their workshops. Besides, local newspapers that are distinct for each area are being used to promote the workshops. However, these older adults move around; and so, some who live in the Control Area may become aware of the campaign and may want to participate in the workshops. There is therefore a risk of contamination of the study.

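### The number of registration calls cannot be compared fairly between the Test and Control Areas, because contact runs in opposite directions and no denominator is given

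*Protocol article*

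**What the plan says.** Under Evaluation Criteria the article defines the primary endpoint: "The primary endpoint is the attendance rate of the participants in the Balance Workshop sessions for fall prevention". It continues: "The secondary evaluation criteria are the number of calls received for a registration request", followed by change in SF-36 and change in IPAQ. Nothing attaches the call count to a population, a number of workshop places or a period, and no separate rule is given for the Control Area.

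The two recruitment sections differ:

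- **Recruitment in the Test Area, Selection.** People who have seen the advertisement approach two partner organisations to register, "through the contact details provided alongside the advertisements".
- **Recruitment in the Control Area, Selection.** After an opening phrase likening the process to ordinary workshop registration, the text says that "the FFPEVG of the Rhône will contact older people who meet the inclusion criteria".

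Design and Setting names Loire and Haute-Loire as Test and Rhône as Control.

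Other text touches on uptake. The first secondary objective is "to increase the participation rate in the Balance Workshop sessions". Recorded Variables lists "Attendance and participation rates in the workshops" among the information collected on participants. The Discussion foresees data on intention to take part, and a statistical evaluation of whether the campaign does better in the Test Area than in the Control Area. It also discloses that "those who will run the program particularly in the Control Area, may have to make more efforts to increase participation in their workshops".

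**The concern.** A communication campaign acts first on who comes forward. The Discussion accordingly poses two questions: whether social marketing brings older adults into the workshops, and whether they then keep attending. The primary endpoint addresses only the second, because it is measured in people who have already joined. Of the criteria listed under Evaluation Criteria, only the call count bears on the first.

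Inbound contact is the described way to register in the Test Area. In the Control Area the described first contact comes from the provider. A count of calls received then depends on which procedure an area uses, as well as on how many people want to register. With no denominator, it also depends on how many older residents each side contains. A reader shown more calls in the Test Area could take the difference for a campaign effect when part or all of it comes from these two sources.

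**Working it through.** **Step 1. The plan's own figure.** There is none for calls. The only sizing figure, 105 + 105 = 210, belongs to the primary endpoint (43% versus 63% of registrants completing) and has no bearing on the call count.

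**Step 2. The recruitment descriptions side by side.**

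| | Test | Control |
|---|---|---|
| Areas | Loire, Haute-Loire (2) | Rhône (1) |
| Who makes first contact | Resident | Provider |
| Route | Contact details printed with the advertisement | Provider's approach; no inbound route described |
| Body handling contact | Two partner organisations | FFPEVG of the Rhône |
| Denominator for calls | None stated | None stated |

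No common counting point for calls is stated.

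**Step 3. What a raw ratio of calls would contain.** For each side, let N be the number of residents aged 60 and over, r the rate at which they wish to register during the period, and s the share of that interest that arrives as a counted inbound call. Then

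expected calls = N × r × s, and

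ratio of calls (Test/Control) = (N_T/N_C) × (r_T/r_C) × (s_T/s_C).

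The quantity of interest is r_T/r_C. Set it to 1, meaning no campaign effect on interest. The documents give neither N nor s, so the values below are assumptions chosen to show a range. The value N_T/N_C = 2 corresponds to three areas of equal population.

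| N_T/N_C | s_T/s_C = 1 | s_T/s_C = 2 | s_T/s_C = 10 |
|---|---|---|---|
| 0.5 | 0.5 × 1 = 0.5 | 0.5 × 2 = 1 | 0.5 × 10 = 5 |
| 1 | 1 × 1 = 1 | 1 × 2 = 2 | 1 × 10 = 10 |
| 2 | 2 × 1 = 2 | 2 × 2 = 4 | 2 × 10 = 20 |

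Over this assumed range the ratio runs from 0.5 to 20 with no campaign effect. Area size can push it either way. The contact route as described pushes it towards the Test Area.

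**Step 4. Whether another stated measure fills the gap.**

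- Attendance is conditional on having joined.
- Enrolled numbers are planned at 105 per area, so they follow the target and cannot show uptake.
- Participation rates are recorded but not defined, are collected on participants, and are not among the listed criteria.
- Intention to take part appears only in the Discussion, not as a listed criterion.

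These data may help with interpretation. None is a stated between-area endpoint for uptake.

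**Step 5. Whether registrations would be better.** Registrations per resident remove N. Because they are counted at a common point whoever made first contact, they largely remove s as well. They do not remove differences in recruitment effort or in workshop capacity (the Discussion foresees new workshops in the areas of intervention), nor the effect of the enrolment target. With two Test areas and one Control area, a model-based rate ratio cannot separate the campaign from other differences between areas.

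**The case against.** The article never says outright that calls will be compared between areas. They could be meant as a process measure of the campaign, which is the use recommended here. This stands as an ambiguity. However, the criterion is listed without restriction beside the other endpoints, and a Test versus Control evaluation of the campaign is announced, so a comparison of calls is a natural reading that the text should rule out.

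A denominator is the kind of detail an article may leave to the full protocol or analysis plan. That is fair, and the lack of a denominator alone would be weak. The opposed contact directions are stated in the article itself and do not depend on omitted detail.

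The first secondary objective may mean participation in sessions rather than uptake in the population. That reading is possible, so the point does not rest on that objective.

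Four stronger readings are tempting, and the documents do not support them:

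- **That Control Area calls would be about zero and the ratio unbounded.** The opening phrase of the Control Area selection text is ambiguous and may cover the usual registration route. The Discussion also accepts that Control Area residents may learn of the campaign and wish to join. Nothing excludes inbound calls there. Likewise, the Test Area text speaks of contact; that this means telephone calls is inferred from the endpoint's name.
- **That the measure favours the Test Area whatever happens.** A larger Control population, or more calls there, would work the other way.
- **That uptake is wholly unmeasured.** Participation and intention data are foreseen, though neither is defined as an endpoint.
- **That the Discussion's remark on extra Control Area effort is a recruitment rule, or should be struck out.** It is a disclosed limitation of uncertain meaning, and deleting it would remove a disclosure without changing conduct.

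**Conclusion.** The point holds in a limited form. If calls are compared between areas, the comparison is confounded by recruitment procedure and area size, and calls are the only uptake-type measure among the listed evaluation criteria. The size of the distortion cannot be derived from the documents. The factor of 2 for two areas against one rests on equal populations and equal call rates, and the wider range shown rests on assumed values.

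The conclusion assumes that the two selection texts describe the actual contact routes and that a between-area reading of calls is intended or likely. The matter concerns one secondary criterion, for which no hypothesis or sample size is stated. The primary endpoint and its 210 participants are untouched. It is worth correcting because the correction is cheap and the uncorrected figure is easily misread as a campaign effect.

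**What to change.** 1. Reword the criterion so that calls received are a descriptive process measure in the Test Area only.
2. For any Test versus Control statement on uptake, use new registrations taken from registration lists. Count them the same way in all three areas over one fixed period, and express them per resident aged 60 and over or per workshop place offered.
3. Log the recruitment route and the provider's outbound contacts in the Control Area, so that effort can be reported beside the registrations.
4. Show the three areas separately and present any rate ratio as descriptive. State that there are only three areas and that registrations still depend on recruitment effort, capacity and the enrolment target.
5. Keep the Discussion's limitation, and add a sentence saying whether Control Area recruitment effort will differ from usual practice.

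The cost is a change of endpoint wording, counts from registration lists, public population figures or the number of places offered, and a simple contact log in the Control Area. The sample size and the primary analysis do not change.
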